## Methods/design

### Aim and study setting

In this multi-site cohort study, we aimed to determine the natural history of the disease; clinical features and management, epidemiological characteristics, immunological, virological courses and treatment response of the disease, effects of diets on the nutritional status on the disease progression, effect of the disease on pregnancy and birth outcomes, and the effect of traditional/modern treatment on COVID-19 outcomes among patients admitted to treatment centers in Ethiopia. Therefore, the study findings will generate scientific data for a systematic understanding of natural history, epidemiological characteristics, clinical features, and management of COVID-19 which will, in turn, enable the country’s health sector to develop strategies to prevent and control the pandemic before it poses further health and socioeconomic crises. The research question of this study is “Do different individual host factors and environmental situations influence clinical, epidemiological, and viral outcomes of COVID-19 infection?”.

The study will be conducted in all Federal treatment centers, including Ekakotebe, Yekatit-12, St. Peter Specialized hospitals, SPHMMC, Millennium hall center in Addis Ababa, and Regional Hospitals including Mekelle, Semera, Bahir Dar, Adama/Mojo, Hawassa, Jijiga, Harar, DireDawa, Metekel or Benishangul Gumuz, and Gambela dedicated to COVID 19 treatment.

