### Study population

This study will enroll individuals with confirmed infection with COVID-19 at selected Federal and Regional Hospitals irrespective of their differences (age, sex, symptoms, severity, and any other conditions). The patients' follow-up will be done strictly within the management adapted to their infection.

Individuals/patients in the study hospital or area will be eligible for inclusion if they meet the following criteria: (1) patient is admitted to selected treatment centers (Federal and Regional’s Hospitals) with COVID-19 confirmed by RT-PCR; and (2) consents to be enrolled in the follow-up study and provide all necessary information/data, blood sample, and nasopharyngeal swab for testing. Patients will be excluded if: (1) a subject deprived of freedom, subject under a legal protective measure; (2) refusal by a participant, parent or appropriate guardian or representative; (3) not willing to stay 12 months in the cohort in Ethiopia; (4) is already involved in the COVID-19 clinical trial or other interventional studies; (5) not capable of understanding or complying with the study protocol or provide consent; (6) anticipated transfer to another hospital that is not a study site within 72 h.

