### Primary outcome and secondary outcomes

The primary outcome variables are treatment outcome (active cases, recovered, death or transferred for further treatment), recovery time, and duration of viral shedding (the time from the first positive RT-PCR results to the occurrence of the last positive RT-PCR results or negative RT-PCR results). The secondary outcomes include clinical symptoms and signs (major); co-morbidities; status at last follow-up (survival, severity, virus detection); laboratory biomarkers; duration of symptomatic phase, inpatient stay, ICU stay; viral loads; anti-SARS-CoV-2 antibody titer; imaging with results; therapeutic measures; plasma 25-hydroxyvitamin D concentrations; dietary history; micronutrient status (zinc and vitamin A); fasting blood sugar; weight, height, BMI; total cholesterol (TC), triglycerides (TG), HDL-C, LDL-C and body composition(waist circumference); genetic frequency shifts (genotypic variations); obstetric and gynecologic history; pregnancy status/test; clinical status; supplemental oxygen; non-invasive ventilation or oxygen delivery devices/ respiratory support. We will also collect confounding variables include socio-demographic variables (age, sex, education status); status cases at the time of enrollment; and months after the first positive test.

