### Data collection

Data collection will be done electronically using the REDCap software package and data documentation will be performed from a retrospective history of the patient and prospectively after treatment is finalized. Contact information such as home address and telephone number will be collected to facilitate follow up and for tracking defaulters of follow-up. For asymptomatic cases whose follow-up is undertaken at home, their home address, GPS coordinates and geospatial data for all participants will also be registered by trained data collectors (study nurse or doctor). Data will be gathered from patients and follow up cases through interviews by physicians/nurses at each treatment center using a questionnaire and standardized Case report form (CRF). Biological samples will also be collected at baseline and follow up when samples are taken in the context of care to meet the research objectives. Five-milliliter venous blood will be collected using a serum separator tube and 4 mL venous blood will be collected using a test tube containing anticoagulant. Viral load measures in a body fluid using Abbot and Rosh reagents and platforms will be measured. Phylogenetic analysis of SARS-CoV-2: genotyping of different types of SARS-CoV-2 from Ethiopian isolates under different settings will be done using a next-generation sequencer at Ethiopian Public Health Institute (EPHI). Imaging: chest x-ray, ultrasound scan, chest computed tomographic (CT) scans data will be retrieved if available. Laboratory tests for D-dimers, platelet count, PT, PTT, INR, D- Dimer, and serum ferritin will be measured.

The screening will be performed within the period between one to two days of admission to the hospital to review study inclusion/exclusion criteria; obtain prior medical and concomitant medication histories; perform a complete physical examination, including height, body weight, and vital signs (blood pressure, BP, heart rate, HR), Oxygen saturation (SpO2) with pulse oximetry; and collect a blood sample for laboratory testing on screening day.

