### Baseline assessment

The baseline assessment (day 1) will be scheduled immediately after screening. At baseline, the following tasks will be performed:Review and record all prior workup or test results.Record detailed history of prior medication use in the subject.The query for signs and symptoms and updated medications used since the screening visit. Any signs or symptoms reported after study drug administration should be recorded as adverse events. Any signs or symptoms reported before the study should be recorded as a pre-existing condition but should be collected and recorded in detail.Perform a complete physical examination.Obtain vital signs (HR, BP, RR, Oxygen saturation, capillary refill), Oxygen saturation (SpO2) with pulse oximetry.Obtain body height, weight, and waist circumference.Obtain the dietary history of the patients.Collect urine for urinalysis, with the microscopic exam and for a pregnancy test (in women).Collect blood for CBC and for serum chemistries including creatinine, total bilirubin, albumin, ALT, AST, total protein, CK, Creatinine Clearance (CrCl), and Ab assays, fasting blood sugar, lipid profiles (TC, LDL, HDL and triglycerides), plasm 25-hydroxy vitamin D concentration, laboratory test for D-dimers, platelet count, PT PPT, INR, and serum ferritin.Collect serum (recommend 5 mL serum storage at the investigational site as a back-up specimen).

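### The aim is worded as an effect of traditional/modern treatment, but because the cohort starts at hospital admission it cannot recover the effect of remedies used before admission

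*Protocol article*

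**What the plan says.** The closing paragraph of the Background and the section Aim and study setting both list, as the last of several aims, determining "the effect of traditional/modern treatment on COVID-19 outcomes among patients admitted to treatment centers in Ethiopia".

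The section Study population sets the first inclusion criterion: "patient is admitted to selected treatment centers (Federal and Regional’s Hospitals) with COVID-19 confirmed by RT-PCR". Patients of any age and severity may enter once admitted, and "The patients' follow-up will be done strictly within the management adapted to their infection". No traditional-only, untreated or community comparison group is described.

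At baseline, staff are to "Record detailed history of prior medication use in the subject". The confounders listed under Primary outcome and secondary outcomes are "socio-demographic variables (age, sex, education status); status cases at the time of enrollment; and months after the first positive test". Data processing and statistical analysis plans bivariate screening, then multivariable and multilevel models. It does not mention selection into admission.

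**The concern.** The aim is causal in wording, while the entry rule sits downstream of part of the exposure. Two contrasts involving traditional remedies are available in this cohort: use before admission, and use alongside hospital care. Neither is a comparison of traditional with modern treatment.

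Use before admission is the harder case. A remedy, or the habits of people who use it, may influence whether a person becomes severely ill and whether a mildly ill person comes to hospital. Both influence admission. Comparing users with non-users among the admitted therefore conditions on something that follows the exposure. The words limiting the aim to admitted patients define the target population, but they do not remove this problem.

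The Discussion says that the results will support policymakers. A figure reported as the effect of traditional treatment could mislead them, either by suggesting harm from an inert remedy or by hiding a benefit.

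**Working it through.** The article gives no figure for this aim, so there is nothing to reproduce. The check is a two-stratum model of who is admitted.

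**Inputs, all assumed for illustration.** A share s of infections is severe: 10% in non-users. Severe cases are admitted with probability 0.95. Mild cases are admitted with probability a. Death risk is 28% if severe and 0.5% if mild, the same for users and non-users. The 28% borrows the sample-size death rate, which the article does not tie to severe cases.

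**Formula.** Death risk among admitted = [s × 0.95 × 0.28 + (1 − s) × a × 0.005] / [s × 0.95 + (1 − s) × a].

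**Non-users**, s = 0.10, a = 0.50: 0.02885 / 0.545 = 5.3%.

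**Users of a remedy with no effect**, s = 0.10:

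| Mild users admitted | Death risk among admitted users | Crude risk ratio |
|---|---|---|
| 50% (equal) | 0.028850 / 0.545 = 5.3% | 1.00 |
| 45% | 0.028625 / 0.500 = 5.7% | 1.08 |
| 40% | 0.028400 / 0.455 = 6.2% | 1.18 |
| 35% | 0.028175 / 0.410 = 6.9% | 1.30 |
| 25% | 0.027725 / 0.320 = 8.7% | 1.64 |

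If 30% of mild non-users are admitted (0.02795 / 0.365 = 7.7%), then 25% of mild users gives 8.7% / 7.7%, a ratio of 1.13. Taking 15% of mild users gives 0.027275 / 0.230 = 11.9%, a ratio of 1.55.

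**Users of a remedy that prevents 20% of severe disease**, s = 0.08. Among all infected people the true ratio is (0.08 × 0.28 + 0.92 × 0.005) / (0.10 × 0.28 + 0.90 × 0.005) = 0.0270 / 0.0325 = 0.83.

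| Mild users admitted (non-users 50%) | Death risk among admitted users | Crude risk ratio |
|---|---|---|
| 50% (equal) | 0.02358 / 0.536 = 4.4% | 0.83 |
| 45% | 0.02335 / 0.490 = 4.8% | 0.90 |
| 40% | 0.02312 / 0.444 = 5.2% | 0.98 |
| 35% | 0.02289 / 0.398 = 5.8% | 1.09 |
| 25% | 0.02243 / 0.306 = 7.3% | 1.38 |

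**Adjusting for severity at enrolment.** Within the severe stratum the risks are 28% and 28%; within the mild stratum, 0.5% and 0.5%. The stratified ratio is 1.00 in every row of both tables. That is right for the inert remedy. It is wrong for the beneficial one, because severity at admission is the route by which that remedy works.

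**Other inputs.** A second set fixes death among admitted non-users at 28%, with 1% in mild cases, 40–70% of infections mild, and mild non-users admitted with probability 0.5–0.9. For an inert remedy the crude ratio is 1.00 with equal admission. It is 1.07–1.20 if mild users are admitted 0.75 times as often, 1.14–1.51 at 0.5 times and 1.23–2.03 at 0.25 times. This set needs a death risk of 38–88% in severe cases, so its upper end is strained. The direction and the condition are the same.

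**The case against.** The strongest reply is that the article does not plan a crude comparison. It lists status at enrolment as a confounder and plans multivariable models. Status is not defined there, but the same section describes status at last follow-up in terms that include severity, so reading it as severity is fair. Under that reading the bias for an inert remedy disappears in the model above. This stands. A reader might infer from the crude ratios that the planned analysis would reverse the sign of a real benefit; the documents do not support that. In this model, adjustment would hide the benefit, not reverse it.

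The direction of the crude bias also depends on differential admission, which the article does not show. Home recoveries are excluded for non-users too, so their absence alone creates no bias.

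Three further inferences go too far:

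- That users enter mainly once severely ill. In the null scenarios, severe cases make up 0.095 / 0.500 = 19% to 0.095 / 0.230 = 41% of admitted users, so most are mild.
- That nobody receives traditional treatment alone. The article does not say what every patient receives, and it mentions asymptomatic patients followed at home ("For asymptomatic cases whose follow-up is undertaken at home"). That remark opens no entry route for people who were never admitted.
- That the lack of a named traditional-remedy item is an error. A condensed article may leave this to the case report form.

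Finally, the phrase traditional/modern may simply mean treatment of either kind, and the aim is one of several. This limits the weight of the point. It does not make the effect of pre-admission use estimable.

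**Conclusion.** The concern holds in a limited form. The aim is stated as an effect, but for remedies used before admission the cohort cannot identify one. The crude comparison is biased if mildly ill users are admitted less often than mildly ill non-users: a ratio of about 1.1 to 1.6 for an inert remedy under the first set of inputs, and 1.00 if admission is equal. The severity-adjusted comparison removes that bias in the simple model, and with it any benefit that works by preventing severe disease. A benefit acting only after severe disease is established would not be lost in this way.

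The sizes rest on assumed inputs. The structural conclusion rests only on the stated aim, the admission criterion and the order of exposure and entry. Use of remedies alongside hospital care remains open to analysis. The point affects one secondary aim, not the primary outcomes, but it changes what the study may conclude about traditional treatment.

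**What to change.** 1. Restate the aim, in the Background and in Aim and study setting, as the association of traditional-remedy use alongside hospital care with outcomes among admitted patients. Make no causal claim of traditional versus modern treatment.
2. Report remedy use before admission descriptively only.
3. Analyse in-hospital add-on use against no add-on use as a time-dependent exposure, adjusted for severity when that use starts.
4. Confirm that the records hold the remedy with start and stop dates, so that use before and after admission can be separated. If they do not, add the item.

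The cost is a change in the wording of the aim, one analysis sentence and, if not already collected, one dated item on the case report form. It needs no additional patients. The downside is a narrower claim. To keep a claim about pre-admission use, the study would have to enrol confirmed cases at testing whether or not they are admitted, which is a much larger change to the design.

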### Study design and period

A multi-center prospective open cohort study design on COVID-19 confirmed cases in Ethiopia conducted from December 01, 2020 to December 2021. Like many other disease-specific general open cohorts, such as in Framingham Heart Study and the Ethiopia Netherlands AIDS Research Project (ENARP) studies, the study intends primarily to measure the incidence of several epidemiological, clinical, virological, and immunological outcomes of COVID-19 cases [29, 30]. The cohort will be an unbiased extensive routine collection of clinical, radiographic, laboratory, and clinical management, virological, immunological and nutritional data, which helps to detect and address emerging research priorities without relying on a priori hypothesis.

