**Methods:**

A multi-center cohort study design will be performed. Patients with confirmed COVID-19 infection admitted to selected treatment centers will be enrolled irrespective of their symptoms and followed-up for 12 months. Baseline epidemiological, clinical, laboratory and imaging data will be collected from treatment records, interviews, physical measurements, and biological samples. Follow-up data collection involves treatment and prognostic outcomes to be measured using different biomarkers and clinical parameters. Data collection will be done electronically using the Open Data Kit (ODK) software package and then exported to STATA/SPSS for analysis. Both descriptive and multivariable analyses will be performed to assess the independent determinants of the treatment outcome and prognosis to generate relevant information for informed prevention and case management. The primary outcomes of this study are death/survival and viral shedding. Secondary outcomes include epidemiological characteristics, clinical features, genetic frequency shifts (genotypic variations), and nutritional status.

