## Background

On March 11, 2020, the World Health Organization (WHO) declared Corona Virus Disease (COVID-19) to be a pandemic [1]. The current new emerging virus is a different strain of virus from SARS and MERS CORONA viruses. The difference is not only limited to genetic makeup but also in the clinical presentations, case fatality, and the rate of spread across the globe (surveillances). The swift spread of the virus is largely attributed to its stealth transmission, for which infected patients may be asymptomatic or exhibit only flu-like symptoms in the early stage. These undetected transmissions present a remarkable challenge for the containment of the virus and pose an appalling threat to public health [2]. COVID-19 has become one of the leading causes of mortality around the world.

As of August 03, 2021, there have been 200,508,148 confirmed cases and 4.26 million deaths reported worldwide and nationally 281,300 confirmed cases and 4,395 deaths reported [3]. To this end, the COVID-19 Global Research and Innovation Forum recommended each country and region to conduct research and generate evidence in their respective local context to strike the right balance between stopping transmission now and prepare for the future [4].

COVID-19 has also sparked fears of an impending economic crisis and recession [5]. Social distancing, self-isolation and quarantine, travel restrictions and border shut downs have led to a reduced workforce across all economic sectors and caused many jobs to be lost. Schools have been closed down, and the need for commodities and manufactured products has decreased [6]. Along with its high infectivity and fatality rates, there has been mass fear of COVID-19, termed as “coronaphobia”, that has generated a plethora of psychiatric manifestations across the different strata of the society [7]. The COVID-19 itself, multiplied by forced quarantine to combat the disease applied by nationwide lockdowns can produce acute panic, anxiety, obsessive behaviors, hoarding, paranoia, depression, and post-traumatic stress disorder (PTSD) [7, 8].

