### Sample size and sampling procedures

The estimated sample size for this study is 6,390, based on the assumptions of a 28 percent death rate from a retrospective study, a design effect of 2.5, and a 20 percent loss to follow-up. A baseline evaluation or assessment will be performed immediately after screening. After baseline assessment, all patients will be followed-up daily until discharge according to WHO and National discharging guideline and followed as per schedule after discharged. Study subjects enrolled will be followed up for 12 months after enrollment for the specific objective related to virology and immunology, clinical course of the disease, response to treatment, effect of COVID-19 in pregnant mothers and birth-related effects of COVID-19. Enrolled cases will be followed up at 2 weeks, 3 months, 6 months, 9 months, and 12 months post-discharge. A visit window of ± 7 days may be applied to these visits. Patients discharged after recovery will be followed up according to the follow-up schedule.

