## Data Availability

As this study is not started, data are not available at this time. De-identified data will be available after publication of primary analyses, upon communication with the corresponding authors and according to the requirements of applicable IRBs and institutional policies.

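### The stated study period of 12 to 13 months cannot hold rolling enrolment plus 12 months of follow-up for most patients

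*Protocol article*

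**What the plan says.** Study design and period describes "A multi-center prospective open cohort study design on COVID-19 confirmed cases in Ethiopia", "conducted from December 01, 2020 to December 2021". The day in December 2021 is not given, and no separate enrolment period or later end of follow-up appears.

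The follow-up promise is made in several places:

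- The abstract (Methods) says patients "will be enrolled irrespective of their symptoms and followed-up for 12 months".
- Study population excludes anyone unwilling to remain in the cohort for 12 months.
- Sample size and sampling procedures says "Study subjects enrolled will be followed up for 12 months after enrollment", there tied to a list of objectives.
- The same section then says "Enrolled cases will be followed up at 2 weeks, 3 months, 6 months, 9 months, and 12 months post-discharge", and adds: "A visit window of ± 7 days may be applied to these visits".
- Follow-up visits gives the same schedule and says these visits serve to ascertain primary and secondary outcomes. They include spirometry, antibody tests, swabs for PCR and dietary history.

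The planned sample size is 6,390, with a 20% allowance for loss to follow-up. Data Availability states: "As this study is not started, data are not available at this time". The Background cites case counts "As of August 03, 2021".

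**The concern.** A cohort that enrols patients over time and follows each for 12 months must run for the length of accrual plus 12 months. This one is given 12 to 13 months in total, so almost nothing is left for accrual if every patient is to complete follow-up.

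The measures at stake exist only if the visit takes place. Survival models accept patients whose observation stops at study closure. A 12-month antibody level, lung-function test or dietary history that falls after closure is simply never taken. The article would then advertise a 12-month cohort, and exclude patients unwilling to stay that long, while its own dates deliver 12-month data on a minority.

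**Working it through.** **Inputs from the article.** Start 1 December 2020. End between 1 December 2021 (365 days) and 31 December 2021 (395 days). Visits at 6, 9 and 12 months, taken as 183, 274 and 365 days. Window of 7 days either side, with the early edge as the favourable case.

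**Assumptions, because the article gives no figure.** Hospital stay 0 to 21 days; a stay of 0 also represents the clock that starts at enrolment. Uniform accrual over the whole period, over 6 months (183 days) or over 3 months (91 days). No deaths or dropout.

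The article's one calculated figure, 6,390, has no stated margin or confidence level, so it cannot be reproduced from the inputs given. The calendar check does not depend on it.

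**Formula.** Last enrolment day that still allows the visit = T − v − stay + (0 or 7), where T is the length of the period and v the visit day. Share able to reach the visit = that number of days ÷ length of accrual, held between 0 and 1.

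**Month 12**

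- End 31 December 2021, no stay, no window: 395 − 365 = 30 days, so enrolled by 31 December 2020; 30/395 = 7.6%.
- The same with the 7-day window: 37 days, so by 7 January 2021; 37/395 = 9.4%.
- The same with a 14-day stay and no window: 395 − 365 − 14 = 16 days; 16/395 = 4.1%.
- End 1 December 2021, no stay, with the window: 7 days; 7/365 = 1.9%. Without the window, or with a stay of 7 days or more: 0%.
- Accrual finished in 3 months, best case: 37/91 = 41%.

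**Month 9, accrual over the whole period**

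- Best case: (395 − 274 + 7)/395 = 128/395 = 32%.
- Worst case: (365 − 274 − 21)/365 = 70/365 = 19%.

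**Month 6, accrual over the whole period**

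- Best case: (395 − 183 + 7)/395 = 219/395 = 55%.
- Worst case: (365 − 183 − 21)/365 = 161/365 = 44%.

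| Assumed accrual | Can reach month 6 | Can reach month 9 | Can reach month 12 |
|---|---|---|---|
| Whole period | 44–55% | 19–32% | 0–9% |
| 6 months | 88–100% | 38–70% | 0–20% |
| 3 months | 100% | 77–100% | 0–41% |

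**How early enrolment must close.** With an end of 31 December 2021, everyone can reach month 9 if enrolment closes between 11 March 2021 (21-day stay, no window) and 8 April 2021 (no stay, with window). With an end of 1 December 2021 the matching dates are 9 February and 9 March 2021. For even half of 6,390 to be able to reach month 12 in the best case, 3,195 patients would have to be enrolled in the first 37 days, or 3,195/37 ≈ 86 a day.

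**Study end that the promise implies.** From 1 December 2020, before any hospital stay is added: about March 2022 with 3 months of accrual, June 2022 with 6 months, December 2022 with 12 months.

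**The case against.** The best defence is that the accrual pattern is unknown. A condensed article may leave the enrolment timetable to the full protocol, and December 2021 may have been meant as the end of enrolment, in which case nothing is lost. That stands as a limit on the percentages. It does not remove the contradiction, because the text says the study is conducted to that date and gives no other end.

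Several stronger readings are tempting, and the documents do not support them:

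- *No patient can complete 12 months.* Those enrolled in the first days or weeks can, unless the study closes on 1 December and the window is not used or is taken up by the stay.
- *The 9-month data are lost in any case.* This depends on accrual; with 3-month accrual 77% to 100% could reach month 9.
- *Most patients miss month 6.* Even with accrual throughout, 44% to 55% could reach it.
- *The primary outcomes are compromised.* Treatment outcome and recovery time are largely settled in hospital under daily follow-up. Most viral shedding is assumed to end early too, although the article gives no distribution.
- *The calendar uses up the 20% loss allowance.* The death rate behind the sample size has no stated time horizon, so the allowance is not shown to refer to month 12.
- *Most 12-month values would be imputed.* Data processing and statistical analysis first evaluates the missing-data mechanism and does not say that visits after closure would be imputed. Full information maximum likelihood creates no values, and Cox models accommodate administrative censoring.
- *The study began after 3 August 2021, leaving 150 days and no 6-month visit.* This joins a Background case count to a data-availability line that may have been written at different times. The article states a start of 1 December 2020, and registration in October 2020 fits that. The statements need reconciling, but they are no measure of the loss.

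**Conclusion.** The plan is wrong as written on this point. Its stated period and its follow-up promise cannot both hold for most patients. Under every accrual pattern tried, most 12-month visits fall after the stated end. The month-9 loss is conditional: large if enrolment runs through the period, largely absent if it closed by about March to early April 2021.

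The percentages rest on uniform accrual, stays of 0 to 21 days and no deaths or dropout. Deaths and dropout would only lower the number of 12-month visits made.

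Two smaller inconsistencies belong with it. The 12 months run both from enrolment and from discharge, which differ by roughly the hospital stay. The not-started statement also conflicts with the stated start date.

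**What to change.** Reconcile the study period with the follow-up promise in one of two ways.

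1. State the enrolment window and set the study end at the last enrolment plus 12 months of follow-up, allowing for hospital stay if the visits run from discharge. If December 2021 is the enrolment cut-off, say so and give the true end of follow-up.
2. If the end date cannot move, restate follow-up as running to a common closing date. Limit the 12-month claims, and the 9-month claims if accrual runs through the period, to patients enrolled early enough to reach the visit. Treat visits not reached at closure as administrative censoring, reported separately from the 20% loss to follow-up.

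In either case, say whether the 12 months and the visit schedule run from enrolment or from discharge. Do not impose one time origin on every time-to-event outcome: Primary outcome and secondary outcomes starts viral shedding at the first positive RT-PCR, and that origin should stay. Reconcile the Data Availability statement with the start date.

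The text changes are small. The first route has a real operating cost: visits could run up to about a year longer across some 15 listed sites, although that follow-up is already promised. The second costs no extra visits but means stating a shorter, less favourable follow-up.
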